#### Subgroup analyses

To evaluate the presence of potential effect measure modification due to infant sex, birthweight, and birth length on deworming, interaction terms will be included in separate multivariable linear regression models with the primary outcome, infant mean weight gain. These analyses will examine if there appears to be effect measure modification by sex, birthweight and birth length, and if so, they will estimate the added value of the intervention in potentially vulnerable subgroups. They will also provide insight into whether deworming can improve growth trajectories separately for boys and girls, as well as for infants born with low birthweight and birth length. If effect measure modification is found, results will be reported separately by subgroup.

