### Sample size and power calculations

The sample size is calculated based on the primary outcome, infant mean weight gain between birth and 6 months of age. An estimate of mean weight gain was obtained from data on children aged between 5 and 7 months residing in Belén in 2010. The estimate of 4.24 kg with a SD of 1.01 kg is the weight gain expected in the placebo group. Previous authors have claimed that an infant mean weight gain difference of approximately 500 g is clinically meaningful from trials on enriched formula feeding in infants.^36^
^38^
^39^ However, since the intervention for the proposed trial is given to women rather than infants, and since there is the possibility for effect dilution (ie, treating both STH infected and non-infected mothers), a mean weight gain difference of at least 200 g is expected between the two intervention groups. This difference in infant mean weight gain is also considered to be clinically significant.^40^

The sample size calculation is, therefore, based on an expected effect size of 0.2 kg and a SD of 1.01 kg, a significance level (α) of 0.05 and a power (1-β) of 0.80. As informed by a previous study in the same hospital population,^41^ the final sample size takes into account a 20% loss to follow-up. Based on the above specifications and a two-sided independent t test, we estimate that 1010 participants is the total sample size needed to declare that infant weight gain is different between intervention groups.

This trial will have sufficient power to detect a difference in proportions as low as 4% for moderate/heavy STH intensity (control group: 6% vs experimental group: 2%),^17^ as well as differences in species-specific STH infection (ie, hookworm, *Ascaris*, *Trichuris*) and infant morbidity indicators (ie, recent occurrence of diarrhoea, respiratory illness, fever, and ear infection), since the differences in proportions between intervention groups for these outcomes are expected to be even larger.^17^
^42–44^ The study will also have sufficient power to detect a clinically meaningful mean difference of 0.5 in z-scores for weight-for-age, weight-for-height and height-for-age,^45^ and a difference in maternal haemoglobin levels similar to those observed in other studies on anthelmintic administration.^13^
^17^
^46^ Sample size and power calculations were conducted using PS Power and Sample Size Calculations V.3.0 (Copyright 1997 by Dupont and Plummet).

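### Subgroup effects are to be shown only if effect modification is found, in a trial sized for the main effect alone; reporting them whatever the interaction result would be a cheap improvement

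*Protocol article*

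**What the plan says.** In the protocol article, under Statistical analyses, Subgroup analyses, three possible effect modifiers are named: infant sex, birthweight and birth length. For these, "interaction terms will be included in separate multivariable linear regression models with the primary outcome, infant mean weight gain".

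What follows depends on the result in two places. The analyses are to look for apparent modification, "and if so, they will estimate the added value of the intervention in potentially vulnerable subgroups". The section then closes with "If effect measure modification is found, results will be reported separately by subgroup". Between these stands a sentence with no condition, which says the analyses will inform on growth separately in boys and girls and in infants of low birthweight and birth length.

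The section does not say what counts as a finding. It gives no interaction size and no power for an interaction.

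Under Sample size and power calculations, the trial is sized for the overall comparison only: "an expected effect size of 0.2 kg and a SD of 1.01 kg", with "a two-sided independent t test". It adds that "the final sample size takes into account a 20% loss to follow-up" and concludes "we estimate that 1010 participants is the total sample size needed".

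**The concern.** This is a stated reporting rule, so the point is not that something is missing. The rule lets the observed interaction decide whether subgroup effects are shown. Whatever the criterion, if it depends on how large or how significant the interaction looks, the effects that are shown will on average be too large. The lower the power, the stronger this bias.

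A trial sized for a main effect usually has much less power for an interaction of the same size. When nothing is found, the plan provides for no subgroup-specific estimate or interval. A reader who wants to know about girls, or about low-birthweight infants, could not then use subgroup intervals to separate a uniform effect from data too imprecise to tell. Yet the section gives exactly these groups as its reason for the analyses.

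**Working it through.** **Inputs from the protocol article.** Difference 0.2 kg, SD 1.01 kg, two-sided alpha 0.05, power 0.80, 20% loss, total 1010 (Sample size and power calculations); 1:1 allocation (Randomisation). Evaluable infants: 1010 × 0.8 = 808, or 404 per arm.

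**Inputs assumed here.** A finding means two-sided p<0.05. Interaction sizes of 0.2, 0.3 and 0.4 kg. Sex split 50:50. Low birthweight or short length treated as a category of 10-20% of infants.

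**1. The plan's own figure.** n per arm = 2 × (1.96 + 0.84)² × 1.01² / 0.2², which gives 401. Total 802, and 802/0.8 gives 1003. The exact t test gives 402 per arm and 804/0.8 = 1005. Both agree closely with 1010. Power with 404 per arm is 80.4%.

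**2. Standard error of an interaction.** For a subgroup with share f of N infants, SE = SD × √(4/(N f) + 4/(N(1 − f))).

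- f = 0.5: SE = 1.01 × 4/√808 = 0.142 kg, twice the main-effect SE of 1.01 × √(2/404) = 0.071 kg
- f = 0.2: SE = 0.178 kg
- f = 0.1: SE = 0.237 kg

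**3. Power**, from Φ(d/SE − 1.96).

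| Subgroup share | 0.2 kg | 0.3 kg | 0.4 kg |
|---|---|---|---|
| 50% (sex) | 29% | 56% | 80% |
| 20% (assumed) | 20% | – | 61% |
| 10% (assumed) | 13% | 24% | 39% |

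At an even split, the smallest estimate reaching p<0.05 is 1.96 × 0.142 = 0.28 kg, and 80% power needs a true interaction of about 0.40 kg.

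The 0.4 kg case is a natural one for sex. If the effect is confined to one sex and averages 0.2 kg overall, it is 0.4 kg in that sex and zero in the other.

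**4. Exaggeration among estimates that pass** (mean absolute estimate given p<0.05, divided by the true value; 2 million simulated draws).

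- Even split: 1.84 at 0.2 kg, 1.33 at 0.3 kg, 1.12 at 0.4 kg
- 10% share: 2.9 at 0.2 kg, 1.58 at 0.4 kg

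As a check for the even split at 0.2 kg: d + SE × φ(1.96 − d/SE)/power = 0.2 + 0.142 × 0.342/0.290 = 0.37 kg, which is 1.84 times 0.2 kg.

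**5. Sensitivity at 0.2 kg, even split.** With no loss to follow-up (1010 evaluable), power is 35%. If covariates explain 10-30% of the variance (assumed), it is 32-39%. If birthweight or length enters as a continuous term, the SE per SD of the modifier is 2 × 1.01/√808 = 0.071 kg, so power is 29% for a slope of 0.1 kg per SD and 80% for 0.2 kg per SD.

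**The case against.** The plan is careful in several respects. It names three modifiers in advance, confines them to the primary outcome, and uses interaction terms rather than separate tests within each subgroup. Looking at the interaction before splitting the results is a common guard against over-reading subgroups. The criterion for a finding, the exploratory label and the table layout may stand in a full protocol or SAP that is not shown, so their absence from an article is no fault. All of this stands, and it is why the point is minor.

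Three stronger readings are tempting, and the document does not support them.

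- **That power is about 29% even in the best case, so that most results would be hidden.** The even split is the most favourable split, but the document states no interaction size. At 0.4 kg, power is about 80% and the exaggeration about 1.1-fold.
- **That the interaction estimates will be withheld, or a negative test read as no modification.** The text makes the subgroup effects conditional. It says neither of these things, and its sentence on insight into boys, girls and small infants carries no condition.
- **That the rule is p<0.05.** No threshold is given in the section; the 0.05 belongs to the sample size calculation. A looser criterion would show results more often and exaggerate them less.

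The figures for small categories also depend on birthweight and length being dichotomised, which the section does not state for the interaction term.

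What the objection does not remove is the conditional rule itself. The 80% power at 0.4 kg applies to an even split. For a category of 10-20% of infants, power at 0.4 kg is still only 39-61%.

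**Conclusion.** The point holds as a minor reporting improvement. Subgroup effects are made conditional on an undefined finding in a trial whose size was set by the main effect alone. Under the stated assumptions, a true sex interaction of 0.2 kg would get no separate subgroup results about 71% of the time (100% − 29%), and when shown would be overstated about 1.8-fold on average. At 0.4 kg these fall to about 20% and 1.1-fold. The rule works less well for small categories, which are the kind of group the section calls vulnerable.

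The size of the problem thus depends on the true interaction, the subgroup share and the criterion, none of which the article fixes. The direction does not: selecting on the result favours large estimates and leaves no planned subgroup interval when nothing is found. The primary analysis, the sample size and the main conclusion are unaffected.

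**What to change.** Replace the last sentence of Subgroup analyses with:

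*For infant sex, birthweight and birth length, the interaction estimate with its 95% CI and the subgroup-specific mean differences with 95% CIs will be reported whatever the interaction result; these analyses are exploratory, and a non-significant interaction will not be taken as evidence of a uniform effect.*

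Remove the matching condition on estimating the added value earlier in the section, so that the two statements agree. Mean differences with 95% CIs are already the reporting format for the adjusted primary analysis, so this extends the plan's own standard.

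The cost is one more table or forest plot, with no new data and no added participants. The drawback is some risk that readers make too much of individual subgroups; the exploratory label limits it.

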## Dissemination

### Trial registration

The trial is registered with clinicaltrials.gov (NCT01748929).

### Information and informed consent

Prior to the onset of the study, meetings at health centres and the Hospital were held to inform the staff of the purpose of the trial, anticipated benefits and risks of participation, and study activities.

Written informed consent documents for participation in the trial were reviewed by the Research Ethics Boards of the McGill University Health Centre in Canada, and the Asociación Civil Impacta Salud y Educación and the Instituto Nacional de Salud in Peru. This document is written in Spanish at a basic literary level and describes the study with respect to its aims and expected contributions, the extent of participant involvement, potential benefits and inconveniences of participation, confidentiality, and the voluntary nature of initial and continued participation. During the informed consent procedure, research assistants will read the consent document to eligible women and their partners. At this time, women and their partners will have the opportunity to ask questions about the trial. Those who wish to participate in the study will be asked to provide consent by signature or fingerprint. For mothers/fathers under the age of 18 years, assent will be obtained and informed consent will be requested from their parent, guardian or spouse/partner over the age of 18 years. The Instituto Nacional de Salud in Peru requires consent from both mothers and fathers for infant participation in RCTs. Women who do not have a partner or whose partner is absent for an indefinite period of time (eg, works outside of Iquitos) will be asked to sign another document to declare the father's absence, in accordance with Peruvian ethics guidelines. Following informed consent, research assistants will administer a short 10-question evaluation to the mothers and their partners to confirm their comprehension of the document. If the mother/father responds incorrectly to a statement, the research assistant will reinforce the contents of the informed consent document.

### Trial oversight

The Trial Steering Committee consists of the principal investigator and all coinvestigators. This committee will review the study protocol, ensure the trial is being conducted in accordance with the principles of good clinical practice, and appoint three international experts with expertise in deworming, biostatistics, or clinical trial methodology to comprise the Data Safety and Monitoring Committee (DSMC). The DSMC will act in accordance with internationally recognised guidelines, review the protocol prior to study initiation, and evaluate study conduct and the occurrence of adverse events at specific time points throughout the trial (ie, after 50% and 100% of recruitment, and after the completion of each follow-up visit).

### Dissemination of results and data access

The results of this trial will be published in peer-reviewed journals, presented at various national and international fora, and communicated to international agencies, such as the WHO, who have taken a leadership role in developing global health policies pertaining to deworming in high-risk population groups. Following completion of the study, project data will initially be used by the research team to prepare the manuscripts and other standard scientific dissemination products. The final trial data set will be available for consultation and available via direct requests to the principal investigator ([name]).
